#### Primary endpoint characteristics

All new infections of the lungs, the blood stream, the urinary tract and wounds are recorded by an infectious disease specialist. Bacteraemia is further classified by responsible pathogen and as catheter-related blood stream infection versus other bacteraemia.

#### Additional data collection

For mechanistic and exploratory studies, muscle strength testing (> 6 years of age) at several moment during admission will be performed.

Urine (nitrogen / bone metabolism / cortisol metabolites / biomarkers for renal failure; NGAL) and stool samples (biomarkers gut function; citrulline / calprotectin) will be collected on daily basis.

We will also perform standard anthropometric tests, upper-arm and lower-leg circumference, in addition to standard weight and height for age. These analyses will be repeated at the follow-up at 3 and 12 months post-discharge, on condition of obtaining adequate additional funding.

Buccal swabs will be collected at day of admission (day 1), day 2, 4 and 6, and possibly on day of discharge and will be immersed in RNA-later and stored at -80C. Buccal epithelial cell expression of chemokines (CXCL-8, CXCL-9 and CXCL-10) will be measured in by Taqman analysis.

Around 100 strands of hair from the posterior vertex of the scalp will be cut off as soon as possible after admission and this will be repeated after 3 weeks- 2 months if possible.

#### Questionnaires and long term follow-up

Furthermore, as far as practically feasible, every patient is approached just prior to hospital discharge, to complete a validated, semi-structured child health questionnaire (Functional Independence Measure (WEEFIM), Health Utilities Index (HUI) and Child Health Questionnaire (CHQ)).

We also will thoroughly assess long-term clinical outcome. This not only encompasses survival rate 3 years after inclusion in the study. It will also involve a detailed functional and neurocognitive examination, by means of questionnaires such as mentioned above. These analyses will be repeated at the follow-up at 3 and 12 months post-discharge, on condition of obtaining adequate additional funding. This will be organised in the framework of current follow-up consultations of these critically ill children.

#### *Figure Samples.*

*Blood samples are taken upon ICU admission and daily at 06:00h until discharge from ICU, death or end of study. Upon admission three blood samples will be taken; namely two yellow "STOL"-tubes each containing a maximum of 3.5 milliliter blood and 1 purple "EDTA"-tube of 1.8 milliliter blood.*

*During the following days until the patient has left the PICU we will daily take a yellow "STOL"-tube (containing max 3,5 milliliter blood) and a purple "EDTA"-tube (containing 1,8 milliliter blood) for further analyses. On day 3,5 and 7 a 'PAX-tube' (containing 2 milliliter blood) will be collected. In children > 10 kg 1,8 milliliter extra blood (EDTA and heparine) will be collected on 4 selected days.*

*A subset of the samples will be immediately stored on ice for future endocrine measurements. Processed serum and plasma as well as the spun-down blood cells will be frozen and stored.*

*Analyses on the morning sample will include routine clinical chemistry, hematology (Hgb, WBC, TC), and markers of inflammation (CRP), liver function ALT, AST, ALP, GGT, bilirubin total/direct. A number of metabolic, hormonal and inflammatory study analyses will be performed on selected days.*

*The latter comprise, among others, coagulation & fibrinolysis tests, cytokines and markers of oxidative stress.*

*Also on selected days stool (single sample,) urine (5 tubes of 5 mL out of 24 hours' urine collection), 100 strands of hair and buccal swabs will be stored for further evaluation.*

*All whole blood glucose levels are measured on arterial blood using a blood gas analyser on each ICU and are registered for later calculation of glucose metrics.*

#### **18.4 Withdrawal of individual subjects**

Subjects can leave the study at any time for any reason if they wish to do so without any consequences. The investigator can decide to withdraw a subject from the study for urgent medical reasons.

##### **18.4.1 Specific criteria for withdrawal (if applicable)**

Not applicable

#### **18.5 Replacement of individual subjects after withdrawal**

Subjects that withdraw after randomization has been conducted will not be replaced, subjects that have not been allocated and withdraw after signing the consent form but before the start of randomization will be replaced.

#### **18.6 Follow-up of subjects withdrawn from treatment**

A register is kept of all patients evaluated for inclusion and of patients who withdraw from the study. The latter are clinically followed up without their data being analyzed in the study, according to intention-to-treat analysis.

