### ***Blinding of treatment allocation***

Treating physicians and patients cannot be blinded. All outcome assessors, which are investigators not directly involved in the patients care (such as statisticians, laboratory personnel, infectious disease specialists, pathologists and physiotherapists involved in the strength measurement) as well as physicians and nurses in the conventional wards are blinded to treatment allocation.

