### ***General rules of the statistical analysis***

All analyses will be done on intention to treat basis. The analyses will be performed on the whole set of patients and by subgroups of patients based on the primary diagnostic categories used as prognostic factors for stratification and on septic/non-septic groups of patients.

A consort diagram will be reported. The data file will be finalised 90 days after inclusion of the last patient. To assess compliance with the study protocol, the amounts of PN and EN actually given in the two study groups during the intervention window of 7 days will be reported as absolute numbers and percentages of target calories. Discrete variables will be summarised by frequencies and percentages and analysed by (exact) Chi- square test or logistic regression analysis. Continuous variables will be summarised by use of either mean or standard deviations (SD) or median and interquartile range as appropriate and compared using Student's t-test or Mann-Whitney-U test, as appropriate. Time to event analysis will be performed by Cox proportional hazard analysis. All outcomes will be analysed in an uncorrected manner as well as (jointly) corrected for risk factors (type and severity of illness, age, on admission nutritional status and risk scores). *A priori* defined subgroup analyses will be performed for patients admitted to ICU after cardiac surgery as compared with all other patients; for patients with and without sepsis upon admission; for patients with contra-indications for EN on admission or not. For all endpoints, differences will be considered statistically significant whenever the p-value is lower than 0.05 without correction for multiple testing.

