### **21.2 Recruitment and consent**

The study protocol and consent forms will be sent for approval by the Institutional Review Board of the Katholieke Universiteit Leuven and the Erasmus MC (Lokale uitvoerbaarheid) and by the competent Belgian and Dutch authorities (CCMO). Written informed consent is obtained from the parents or the legal guardian by the investigator's team or one of the supervising doctors, who will inform the parents of the patients (and the patients themselves if the age is > 12 years) and ask for their consent. The parents / legal guardians and (if applicable) the patients will receive a patient information letter and an informed consent form.

Written informed consent will be obtained from the patient or the closest family member or legal guardian. For planned PICU admissions after elective procedures, informed consent will be asked beforehand, if possible.

For emergency PICU admissions, treatment allocation will be done after assessment of the patient for eligibility by the attending physician within the time frame of two hours. If eligible, the patient will be randomized into the study and the allocated glucose infusion (with micronutrients) will be started. Informed consent will be asked within the time frame of 24 hours (deferred informed consent) as a nutritional regimen has to be initiated already on admission. When consent is given, the allocated nutritional regimen will proceed (Early (with additional lipids and protein targeting nutritional goals < day3) vs Late (no PN)). When NO consent is given, the nutritional regimen and glucose infusion will be placed under responsibility of the supervising clinical team of doctors.

The parents or legal guardians can withdraw the patient from the study at any time, without penalty or impact on treatment.

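### Section 18.6 leaves withdrawn children out of the analysis and calls this intention-to-treat, contradicting section 20.1; the comparisons could be biased in either direction, by an amount the documents do not fix

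*Supplement*

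**What the plan says.** All references are to the final protocol unless stated.

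- **Section 18.6** keeps a register of patients evaluated and of those who withdraw from the study. Of the withdrawn it says: "The latter are clinically followed up without their data being analyzed in the study, according to intention-to-treat analysis".
- **Section 20.1**, general rules: "All analyses will be done on intention to treat basis". The economic analysis (18.1.2) and the early-mortality analysis (18.1.3, 19 and 20.1) make the same commitment.
- **Section 18.4** gives two routes out. For the family: "Subjects can leave the study at any time for any reason if they wish to do so without any consequences". For the investigator: "The investigator can decide to withdraw a subject from the study for urgent medical reasons". Section 18.4.1 sets no specific criteria.
- **Section 18.5**: "Subjects that withdraw after randomization has been conducted will not be replaced".
- **Section 18.2**, on blinding: "Treating physicians and patients cannot be blinded".
- **Section 21.2**, for emergency admissions: "If eligible, the patient will be randomized into the study and the allocated glucose infusion (with micronutrients) will be started". Consent is then sought within 24 hours. The section does not say how a randomised child is analysed if consent is refused.
- **Section 22.1** has 90-day vital status recorded for all patients, from death registries where necessary.

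The SAP covers a secondary analysis. It reports 1440 children randomised (717 late PN, 723 early PN) and does not mention withdrawals. Neither document has a missing-data rule or a sensitivity analysis for withdrawals.

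**The concern.** An analyst cannot obey 18.6 and 20.1 together. Section 20.1 keeps every randomised child in the allocated arm, while 18.6 takes some out after allocation and gives that the same name. It makes no exception for any endpoint, so as written it reaches infections, time to live discharge and mortality.

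Exclusion after randomisation is harmless only if it is unrelated to prognosis or works alike in both arms. Neither is assured here. The investigator's route in 18.4 depends by its wording on the child's medical condition, has no criteria, and is used by someone who knows the arm. If sicker children leave one arm more often than the other, the remaining groups are no longer those that were randomised. This can work against either strategy: removing sicker late-PN children flatters late PN, and removing sicker early-PN children flatters early PN.

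Withdrawn children are not replaced, and the sample size in 15.4 states no allowance for loss, so exclusions also reduce power.

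**Working it through.** **1. The plan's own figure.** Inputs from 15.4: 720 per arm, infections 20% versus 15%, 5% significance level. Normal approximation with pooled variance under the null:

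- Null standard error: √(2 × 0.175 × 0.825 / 720) = 0.02003.
- Alternative standard error: √((0.20 × 0.80 + 0.15 × 0.85) / 720) = 0.01998.
- One-tailed power: Φ((0.05 − 1.645 × 0.02003) / 0.01998) = 80.3%.
- Two-tailed power: Φ((0.05 − 1.960 × 0.02003) / 0.01998) = 70.5%.

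The stated 80% and 70% are reproduced. The point disputes no figure in the plan.

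**2. Power if withdrawn children are excluded and not replaced.** The loss rates are assumptions, equal in both arms.

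| Loss | Analysed per arm | One-tailed power | Two-tailed power |
|---|---|---|---|
| 0% | 720 | 80.3% | 70.5% |
| 1% | 712.8 | 80.0% | 70.0% |
| 2% | 705.6 | 79.6% | 69.6% |
| 5% | 684 | 78.5% | 68.2% |
| 10% | 648 | 76.6% | 65.9% |

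**3. Bias under no true effect.** Assume 20% infections in both arms. A fraction w of one arm only is excluded, and the excluded children have infection risk q. That arm's analysed rate is (0.20 − wq) / (1 − w), so the spurious difference is w(q − 0.20) / (1 − w).

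Example with w = 5% and q = 60%: 0.05 × 0.40 / 0.95 = 2.1 points. The analysed rate is 17.9% in 684 children against 20% in 720. The pooled rate is about 18.97%, with null standard error 0.02094 and alternative standard error 0.02091. The chance of a nominally significant two-sided result is Φ((0.02105 − 1.960 × 0.02094) / 0.02091) plus the small opposite tail, which is 17.1%.

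| Excluded from one arm | q = 20% | q = 40% | q = 60% |
|---|---|---|---|
| 2% (about 14 children) | 0 points; 5.0% | 0.4 points; 5.4% | 0.8 points; 6.7% |
| 5% (36 children) | 0 points; 5.0% | 1.1 points; 7.9% | 2.1 points; 17.1% |
| 10% (72 children) | 0 points; 5.0% | 2.2 points; 18.1% | 4.4 points; 57.2% |

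Each cell gives the spurious difference and the two-sided rejection probability at a nominal 5%. If the exclusions fall in the other arm, the sign reverses and the size is the same. If both arms lose children in part, the biases offset to the extent that rates and risks agree.

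**The case against.** The strongest reply is that 18.6 is a badly drafted sentence in a plan otherwise committed to intention-to-treat. That commitment appears in several sections, 90-day vital status is recorded for everyone, a register of withdrawals is kept and a CONSORT diagram is promised. The heading of 18.6 concerns leaving treatment but its sentence concerns leaving the study, so a child who merely stops the allocated nutrition may not be meant. Where parents withdraw consent to use of data, exclusion may be unavoidable under any wording.

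Much of this stands as a limit on the point. It does not remove the conflict: the sentence is in the current text, names no exception and is not corrected elsewhere. Recording vital status for all does not help if 18.6 then keeps it out of the analysis.

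Four stronger readings are tempting and are not supported:

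- **That withdrawn children were in fact dropped, or that the result was biased.** The documents conflict on what should happen and do not show what was done. The SAP total of 1440 equals the planned number but does not reveal how withdrawn or non-consenting children were handled.
- **That the bias favours late PN.** Section 18.4 applies to both arms.
- **That refusals of deferred consent fall under 18.6 and would be cured by rewording it.** Section 21.2 does not call refusal a withdrawal, does not refer to 18.6 and concerns emergency admissions. Refused data would still be left out after the change.
- **That the design counts 720 analysed per arm.** Section 15.4 gives 720 per arm without saying analysed.

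**Conclusion.** The contradiction is real, and 18.6 is wrong as written. Its exclusion rule is not intention-to-treat, and with unblinded withdrawal on medical grounds it opens a route to bias in infections, ICU stay and mortality, in either direction.

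The size is unknown. The calculated range runs from no bias, when the excluded have average risk, through less than 1 point at 2% one-sided exclusion, to 4.4 points at 10% with a 60% infection risk. The larger values need dozens of children removed from one arm and none from the other, at two to three times the average risk. Nothing in the documents indicates such numbers, so they show sensitivity and are not a forecast. The loss of power is modest: at 1–2% loss the figures are essentially those stated in the plan.

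The correction is warranted because the analysis population of the primary and mortality comparisons should not rest on a self-contradictory sentence.

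**What to change.** Replace the rule in 18.6 with wording to this effect:

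- Every randomised child is analysed in the allocated arm.
- Stopping the allocated nutrition, or withdrawal by the investigator, neither ends routine data collection nor removes data.
- Only data for which consent to use is refused or withdrawn are left out. Data up to that point, and 90-day vital status, are used where permitted.

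State in 21.2 how randomised children whose parents refuse deferred consent are counted and reported. Report withdrawals and refusals by arm, timing, reason and initiator, building on the existing register and CONSORT diagram. Add a sensitivity analysis that varies the assumed outcomes of excluded children separately by arm. Acknowledge that exclusions for refused consent may be unavoidable and are not removed by this change.

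The cost is protocol wording, one added analysis and continued capture through the existing data management system, case record form and registry linkage. No patients are added, and the stated sample size and power do not change.

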#### **18.7 Premature termination of the study**

As the previous study in adults has shown that lethality was not different among the study groups and that morbidity was prevented by withholding feeding, and since the participating centers are currently providing early PN, repeated interim analyses for efficacy are not required. However, one formal “safety” interim analysis will be planned after patient number 720 has left the ICU, during which the independent DSMB will have access to un-blinded results on ICU mortality, hospital mortality and serious adverse events. The DSMB will then judge on whether or not to prematurely stop the clinical trial for safety reasons, or to perform more safety interim analyses. The DSMB will advise on eventual continuation of the study to completion, under monitoring of the serious adverse event. Because the primary efficacy

endpoint will not be analyzed, no correction of the significance level at the final analysis will be necessary. In (the unlikely) case the study would be terminated prematurely, the mechanistic studies will be even more important, as the clinical community will ask for due explanations for harm caused during the study. Therefore, in any case they will be started shortly after all clinical data have been collected.

## 19. SAFETY REPORTING

The risk in participating to the study and being randomized to the "late PN" group are negligible, and specifically compass an increased risk of developing hypoglycemia and/or underfeeding. However, safety measures will be taken to further decrease these risks. Our study may provide support for current practice, may give "neutral" results for which the cost-effectiveness study will provide necessary information for guiding therapy, or may challenge the presumed innocence of PN. Thus, there is no risk associated with the intrinsic value of these results.

The burden is expected to be minimal as it will only entail additional blood draws, which will be taken from clinical lines or in addition to pricks for clinical purpose. The long-term follow up will be held as part of already organised follow-up outdoor clinics and which are developed to help children and their parents to recover physically, emotionally and socially after ICU admissions. For mechanistic and exploratory studies, muscle strength testing and an ultrasound evaluation of the skeletal muscle and adipose tissue compartments will be performed. Furthermore, as far as practically feasible, every patient is approached just prior to hospital discharge, to complete a validated, semi-structured child health questionnaire (Functional Independence Measure (WEEFIM), Health Utilities Index (HUI) and Child Health Questionnaire (CHQ)).

In order to monitor the quality of the enteral and parenteral nutrition management during the study we will register all known complications possibly related to them. These complications should not be considered as adverse events since the study intervention is to withhold parenteral feeding during one week. These known complications of parenteral feeding will not be reported to the sponsor until the end of the trial.

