### **\*Complications possibly related to parenteral feeding**

Mechanical complications Occlusion and dislodging of central venous catheters

Clinical complications: pneumothorax, hemothorax and arterial puncture, central line replacement due to suspicion of catheter-related blood stream infections

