### Safety endpoints

Safety endpoints comprise vital status, hypoglycaemia, SAEs and complications related to the mode of nutrition. Survival up to 90 days after randomisation in both treatment groups will be compared by Kaplan Meier survival plots. The impact of "late PN" versus "early PN" will be analysed, with and without correction for risk factors, by Cox proportional hazard analysis. In addition, we will record in-ICU and in-hospital mortality, and will analyse differences with Chi-square testing. As the

randomised study intervention only takes place during a time window up to the 8th day in ICU, we also plan to analyse early lethality within this time window in the intention-to-treat population as part of the safety analysis.

As patients not receiving early PN may be considered at increased risk for hypoglycaemia, we will report for both groups the number of patients experiencing hypoglycaemia <40 mg/dl during the time window of the randomised intervention.

Hypoglycaemia resistant to parenteral glucose administration is considered as a SAE and the incidence during the time window of the randomised intervention will be reported for both groups. In addition, overall blood glucose control during the time window of the intervention will be compared using daily morning blood glucose as well as daily maximal and minimal blood glucose.

Safety issues also comprise the occurrence of feeding-mode-related complications during the time window of the intervention. Therefore, occurrence of these complications (digestive intolerance, complicated insertion of feeding tubes, pneumothorax, haemothorax and subclavian or carotid artery puncture, occlusion or displacement of central venous catheters or gastric feeding tubes) will be reported for both treatment groups

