### **19.2 Adverse and serious adverse events**

Adverse events are defined as any undesirable experience occurring to a subject during the study, whether or not considered related to the experimental treatment. All adverse events reported spontaneously by the subject or observed by the investigator or his staff will be recorded.

A serious adverse event is any untoward medical occurrence or effect that at any dose:

- results in death;
- is life threatening (at the time of the event);
- requires hospitalisation or prolongation of existing inpatients' hospitalisation;
- results in persistent or significant disability or incapacity;
- is a new event of the trial likely to affect the safety of the subjects, such as an unexpected outcome of an adverse reaction, lack of efficacy of an IMP used for the treatment of a life threatening disease, major safety finding from a newly completed animal study, etc.

All SAEs will be reported through the web portal *ToetsingOnline* to the accredited METC that approved the protocol, within 15 days after the sponsor has first knowledge of the serious adverse reactions. SAEs that result in death or are life threatening should be reported expedited. The expedited reporting will occur not later than 7 days after the responsible investigator has first knowledge of the adverse reaction. This is for a preliminary report with another 8 days for completion of the report.

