### **Safety endpoints specifically for PEPaNIC**

The clinical research team guarantees a daily follow-up of patient screening and inclusion, availability of requested clinical data in the clinical patient files and protocol compliance. Each non-compliance to the protocol and other questions or problems are reported to the study monitor and discussed with the principal investigators. Serious Adverse Events (SAE) are also reported to the study coordinating investigator/project leader (K.U.Leuven). The study monitor regularly provides the sponsor with reports on inclusions and SAE. Regular meetings are organized with principal investigators and clinical research team to discuss the daily progression of the research project.

As patients not receiving early PN may be considered at increased risk for hypoglycemia, we will report for both groups the number of patients experiencing hypoglycemia <40 mg/dl during the time window of the randomized intervention.

Hypoglycemia resistant to parenteral glucose administration, or with clinical symptoms, is considered as a SAE and the incidence during the time window of the randomized intervention will be reported for both groups. In addition, overall blood glucose control during the time window of the intervention will be compared using daily morning blood glucose as well as daily maximal and minimal blood glucose.

Further safety endpoints comprise vital status, hypoglycemia, SAEs and complications related to the mode of nutrition. Survival up to 90 days after randomization in both treatment groups will be compared by Kaplan Meier survival plots. The impact of "late PN" versus "early PN" will be analyzed, with and without correction for risk factors, by Cox proportional hazard analysis. In addition, we will record in-ICU and in-hospital mortality, and will analyze differences with Chi-square testing. As the randomized study intervention only takes place during a time window up to the 8th day in ICU, we also plan to analyze early lethality within this time window in the intention-to-treat population as part of the safety analysis.

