Safety issues also comprise the occurrence of feeding-mode-related complications during the time window of the intervention. Therefore, occurrence of these complications (digestive intolerance, complicated insertion of feeding tubes, pneumothorax, haemothorax and subclavian or carotid artery puncture, occlusion or displacement of central venous catheters or gastric feeding tubes) will be reported for both treatment groups.

Above mentioned SAE's and safety endpoints will be handled and reported within the standard timeframe as described above.

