#### **20.4 Interim analysis**

As the previous study in adults has shown that lethality was not different among the study groups and that morbidity was prevented by withholding feeding, and since the participating centers are currently providing early PN, repeated interim analyses for efficacy are not required. However, one formal “safety” interim analysis will be planned after patient number 720 has left the ICU, during which the independent DSMB will have access to un-blinded results on ICU mortality, hospital mortality and serious adverse events. The DSMB will then judge on whether or not to prematurely stop the clinical trial for safety reasons, or to perform more safety interim analyses. The DSMB will advise on eventual continuation of the study to completion, under monitoring of the serious adverse event. Because the primary efficacy endpoint will not be analyzed, no correction of the significance level at the final analysis will be necessary.

The safety analyses will be done on the whole set of patients and by subgroups of patients based on the primary diagnostic categories used as prognostic factors for stratification and on septic/non-septic groups of patients.

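### The final protocol gives conflicting rules on whether and when feeding complications are reported and on which hypoglycaemia is an SAE, so the SAE data for the DSMB interim could be incomplete and inconsistently classified

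*Supplement*

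**What the plan says.** All references are to the final protocol.

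**Feeding complications.** The opening of Section 19 has the known complications of enteral and parenteral feeding registered, then states: "These complications should not be considered as adverse events since the study intervention is to withhold parenteral feeding during one week". For the parenteral ones it adds: "These known complications of parenteral feeding will not be reported to the sponsor until the end of the trial". The lists that follow include tracheal aspiration on the enteral side. On the parenteral side they include catheter occlusion and dislodging, and "pneumothorax, hemothorax and arterial puncture, central line replacement due to suspicion of catheter-related blood stream infections".

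Section 19.2 opens with a general definition: "Adverse events are defined as any undesirable experience occurring to a subject during the study, whether or not considered related to the experimental treatment". An event is serious if, among other criteria, it is life-threatening or prolongs a hospital stay. Its trial-specific part counts complications of the feeding mode among the safety endpoints, lists most of the same events, and closes: "Above mentioned SAE's and safety endpoints will be handled and reported within the standard timeframe as described above".

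**Hypoglycaemia.** Section 19, under Safety endpoints, says: "Hypoglycaemia resistant to parenteral glucose administration is considered as a SAE". Section 18.1.3 has the same rule. The trial-specific part of Section 19.2 says: "Hypoglycemia resistant to parenteral glucose administration, or with clinical symptoms, is considered as a SAE".

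**Interim.** Section 20.4 plans one formal safety look after patient 720 has left the ICU, at which "the independent DSMB will have access to un-blinded results on ICU mortality, hospital mortality and serious adverse events". Sections 18.7, 19 and 19.4 repeat this. The DSMB may ask for further safety looks.

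**The concern.** Sites are given two incompatible instructions for the same event, twice over. For a life-threatening pneumothorax, one section says that it is not an adverse event and the other makes it an SAE with an expedited deadline. For an episode of symptomatic hypoglycaemia that responds to glucose, one section names it as an SAE and two do not.

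This matters because SAEs are the only non-fatal data that the protocol names for the DSMB's interim decision to stop, continue or look again. Hypoglycaemia is one of the two specific risks that Section 19 names for late PN; the other is underfeeding. If the content of the SAE data depends on which page a site or assessor followed, the DSMB cannot know whether a low count means few events or a narrow rule.

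**Working it through.** No figure in the plan can be reproduced here. The check is to set the rules side by side and run typical events through them.

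**Feeding complications**

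| | Opening of Section 19 | Section 19.2 |
|---|---|---|
| Adverse event? | No | Yes; the general definition has no exemption |
| Can it be an SAE? | Not if it is not an adverse event | Yes, if a seriousness criterion is met |
| When reported | Parenteral: to the sponsor at the end of the trial. Enteral: no time given | Usual deadlines: 15 days for SAEs; if fatal or life-threatening, 7 days plus 8 to complete |

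The two lists are close but not identical. Line replacement for suspected catheter infection is in Section 19 and absent from the trial-specific list in 19.2. Tracheal aspiration enters the 19.2 list only through digestive intolerance.

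The timing rules also interact. The 15-day period runs from the sponsor's first knowledge of the event. If parenteral complications are not reported to the sponsor before the end of the trial, that period does not start. The 7-day period runs from the investigator's knowledge, so it conflicts with the delay directly.

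**Hypoglycaemia as an SAE**

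| Episode | Sections 18.1.3 and 19 | Section 19.2, trial-specific part |
|---|---|---|
| Resistant to parenteral glucose | SAE | SAE |
| Symptomatic, responds to glucose | Not named as SAE | SAE |
| Below 40 mg/dl, no symptoms, responds to glucose | Not named as SAE | Not named as SAE |

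Only the middle row is in conflict, and only for episodes that do not already meet a general seriousness criterion.

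**What reaches the interim SAE data**

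| Event | Opening of 19 and narrow hypoglycaemia rule | Section 19.2 throughout |
|---|---|---|
| Death | In the mortality data | In the mortality data |
| Life-threatening pneumothorax from a central line | Out | In |
| Arterial puncture meeting no seriousness criterion | Out | Out (adverse event only) |
| Symptomatic hypoglycaemia, responds to glucose, no general criterion met | Out | In |
| Hypoglycaemia resistant to glucose | In | In |

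Two classes of event change status: feeding complications that meet a seriousness criterion, and symptomatic hypoglycaemia that responds to glucose. The look comes at 720/1440 = 50% of planned enrolment.

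**Is the conflict resolved elsewhere?** No. The two amendments add a site, samples and an enteral-tolerance endpoint and leave these rules alone. The SAP covers a secondary analysis. It lists hypoglycaemia in the first week as a safety outcome and has no SAE rule. No section says that one part of the protocol overrides another.

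**The case against.** **The delay concerns the sponsor, not the DSMB.** This is correct, and a reader should not infer that complications are to be hidden from the DSMB; no text says so. But the sentence before it says that these events are not adverse events. On that reading they cannot be SAEs, and they fall outside the SAE data whoever receives them.

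**The general seriousness criteria catch the important cases.** They do if Section 19.2 prevails over the opening of Section 19. The protocol does not say that it does. The objection does establish that the data could be incomplete, not that they would be.

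**No rule differs by arm.** This stands. A reader might infer that the arms would not be comparable: the delay names parenteral complications only, first-week PN belongs to the early-PN arm, hypoglycaemia is a named risk of late PN, and treating physicians are unblinded. These make an imbalance possible. They do not show one. Each wording applies to both groups. The parenteral list consists largely of central-line events, headed as only possibly related to PN, and nothing restricts central lines to one arm. Randomisation is 1:1 within centre, so a centre that follows one text applies it to both arms.

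**Direction.** The stopping scenario in the Study Design section is harm from late PN. If early-PN line complications were under-counted, late PN would look relatively worse, which would not hide that harm. Only the narrower hypoglycaemia wording could.

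**Other safeguards.** The DSMB may request more looks, though that decision would rest on the same data. Hypoglycaemia below 40 mg/dl is to be reported for both groups whatever its SAE status, so the final report is protected on that point.

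**Conclusion.** Both contradictions are present in the final protocol and nothing later resolves them. They are conflicting stated rules, not missing detail. Their consequence is conditional: the non-fatal safety data at the 720-patient look could be incomplete, and could differ between sites or assessors, according to the text followed.

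The size cannot be given as a number, because the documents contain no rates for the two affected classes of event. A reader might argue from low power for mortality at half the sample that the DSMB must lean on SAE counts. That power is the same under either rule, so it does not measure this defect, and no document says how the DSMB weighs its data.

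The conclusion assumes that the interim data follow the content named in Section 20.4; no table layout is given. It does not extend to deaths, the primary endpoints, the sample size or the final count of hypoglycaemia below 40 mg/dl.

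**What to change.** 1. Use one SAE rule for hypoglycaemia in Section 18.1.3, Section 19 and the trial-specific part of Section 19.2. Which rule is a clinical decision for the investigators.
2. Use one rule on whether feeding complications are adverse events and when they are reported, in the opening of Section 19 and in Section 19.2. Align the two lists of events, and say what happens when a listed complication meets a seriousness criterion.
3. State in Section 20.4, and where it is repeated, which of these events enter the interim SAE data.
4. As a low-cost addition, give the DSMB two tables by arm at patient 720: the recorded enteral and parenteral feeding complications, and patients with hypoglycaemia below 40 mg/dl. The interim then does not depend on the classification.

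Items 1 to 3 are protocol wording. Item 4 goes beyond reconciliation but needs no new data: Section 18.3 already has the complications recorded and all blood glucose values registered.
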